### Pain Education

The educational program will be based on the protocol described by Traeger et al [16] and will consist of a biopsychosocial approach to dealing with fears and clarifying behavioral beliefs about pain and movement. Additionally, the program will explain the influence of emotional symptoms (stress, anxiety, kinesiophobia, etc) on chronic pain; the influence of lack of sleep and physical activity on LBP, gradual exposure to physical activity, and daily movements; and the neurophysiology of pain. The program will include the following three major components: (1) clarifying any useless beliefs about the nature of LBP, (2) presenting key concepts of the biology of pain, and (3) evaluating patients’ understanding and discussing recovery. Participants who are randomized to the pain education intervention will participate in two 1-hour sessions of pain education that will be conducted by a physiotherapist. The physiotherapist will be appropriately trained for the study and will be contacted weekly for clarifications on doubts and possible further guidance. Multimedia Appendix 1 shows the 3 steps of the Pain Education Program.

### MCEs and Pain Education

Individuals who are allocated to both interventions will receive guidance regarding the educational program for 1 hour during the first appointment, before participating in the MCE program for 8 weeks. The topics that will be covered throughout the treatment will be reinforced, emphasizing the factors for which individuals have more difficulty with changing their behavior.

### Usual Care Intervention

Conventional intervention will be based on exercises that are usually performed in clinical practice. It will involve the active stretching of the posterior thigh muscles (hamstrings) by using a resistance band. The therapeutic exercises will include (1) isometric exercises that activate the muscles of the core region and stabilizers of the loin-pelvic region and hips (the transverse abdominis and multifidus muscles, oblique and rectus abdominal muscles, gluteus minimus, and gluteus maximus); (2) isotonic exercises for the lower limbs (hip abduction and adduction and hip flexion and extension); (3) exercises that focus on movement functionality, which will be augmented by breathing and body perception techniques, body realignment, and muscular and joint imbalance correction; (4) resistance exercises that involve using an elastic band to strengthen lower limb musculature; and (5) guidance for performing daily life activities and explaining the importance of staying active to prevent recurrence or increases in pain, which will be given spontaneously as an initiative of the responsible physiotherapist.

The exercise interventions will be conducted with groups of 3 patients, and the program will last for 8 weeks. Patients will receive care twice per week, totaling 16 visits. The patients cannot perform any other types of exercises during the study period. To maintain patients’ compliance with the program, researchers will contact them each week to inquire about the progress of the interventions.

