### Recruitment

We will recruit individuals with LBP at outpatient clinics of basic health units in Pelotas, Brazil, while they wait for an evaluation. During recruitment, we will determine their study eligibility based on the inclusion and exclusion criteria in Textbox 1.

Individuals will be randomly allocated to intervention groups, having the same probability of being allocated to a group that will be exposed to the test interventions or the control group.

Inclusion and exclusion criteria.

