### Study Procedures

#### Sample Size Calculation

Sampling will be probabilistic, and patients will be extracted from the LBP waiting list. The required sample size was calculated by assuming a mean difference of 1.5 and an SD of 2.4 [27]; the study requires a sample size of 225 per group, that is, 900 individuals in total.

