#### Random Allocation and Blinding

After the initial evaluation, the participants will be allocated, through block randomization, to receive different interventions, which will be conducted by physiotherapists. Individuals who fulfill the inclusion criteria will receive clarification about the objectives and the procedures that will performed in the research, and their consent will be requested by asking them to sign the informed consent form, of which the terms were approved by the ethics committees of the Federal University of Pelotas and the Health Department of Pelotas City.

The participants will then be referred to the physiotherapist who will be selecting the interventions according to the groups to which the participants will be allocated. The individuals who are allocated to the M-group, MP-group, and U-group will participate in 16 treatment sessions (2 sessions per week, totaling 8 weeks of treatment) with an average duration of 40 minutes.

It will not be possible to blind the physiotherapists who are responsible for the interventions due to the type of research that will be conducted. However, evaluators and patients will be blinded to the treatment groups. Nonblinding conditions will only occur in cases of health emergencies.

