### Statistical Analysis

The data will be analyzed by using SPSS version 20.0 (IBM Corporation). Descriptive statistics (means, SDs, and frequencies) will be used to present the characteristics of the participants, and inferential tests will be used to analyze the differences among the groups. Analyses will be performed based on intent-to-treat principles. The outcomes (Numeric Pain Rating Scale, Roland Morris Disability Questionnaire, Fear Avoidance Belief Questionnaire, Tampa Scale of Kinesiophobia, Short Form-36 Health Survey, Brunel Humor Scale, Beck Depression Inventory, Beck Anxiety Inventory, and Pittsburg Sleep Quality Index scores and the pressure threshold for pain) will be analyzed by using generalized estimation equations to compare the M-group, P-group, MP-group, and U-group at baseline, after 8 weeks, and at the 12- and 24-week follow-ups. The effects of groups, time, and group interactions with time (group×time) will be analyzed. The Bonferroni post hoc test will be used to identify the differences among the means of all variables. Missing data will be handled via multiple imputation [28]. The α established as the level of significance will be *P*<.05 (95%) for all hypothesis tests. The effect sizes will be checked by using the Hedges g test. The magnitudes of effect sizes will be interpreted as *trivial* (<0.2), *small* (0.2-0.6), *moderate* (0.6-1.2), *large* (1.2-2.0), *very large* (2.0-4.0), and *perfect* (>4.0) [29]. To represent the effect of the intervention, the delta (∆) of the analyzed variables (∆ = x ®postintervention − x ®preintervention) will be calculated.

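### Exercise is given in groups of 3, but the stated GEE has no treatment-group level; if patients are its clusters, standard errors for comparisons involving exercise arms are understated whenever the within-group correlation is positive

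*Protocol article*

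**What the plan says.** - **Unit of randomization** (Recruitment): "Individuals will be randomly allocated to intervention groups".
- **Delivery of exercise** (Usual Care Intervention): "The exercise interventions will be conducted with groups of 3 patients", over 8 weeks and 16 visits. The sentence stands under the usual-care heading, but it speaks of exercise interventions in the plural.
- **Arms on that schedule** (Random Allocation and Blinding): "The individuals who are allocated to the M-group, MP-group, and U-group will participate in 16 treatment sessions". Reading the groups of 3 as applying to all three arms is therefore reasonable, though it is a reading.
- **P-group** (Pain Education): its participants "will participate in two 1-hour sessions of pain education that will be conducted by a physiotherapist". Whether these sessions are individual or in groups is not stated.
- **Analysis** (Statistical Analysis): the outcomes "will be analyzed by using generalized estimation equations to compare the M-group, P-group, MP-group, and U-group at baseline" and at 8, 12 and 24 weeks. The effects are then named: "The effects of groups, time, and group interactions with time (group×time) will be analyzed". The section names neither the GEE cluster (subject) variable, nor the working correlation, nor the variance estimator.

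**The concern.** Individuals are randomized, but in up to three of the four arms they are then treated in small groups. People who share sessions for 8 weeks may come to have similar outcomes, through the instructor, the pace of the session or each other. In the U-group there is a specific route: Usual Care Intervention leaves part of the advice on daily activities to the physiotherapist's own initiative, so patients treated together may share advice that others do not get.

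The only correlation that the stated analysis implies is that between repeated measurements on one patient. A robust variance with the patient as cluster protects against misspecifying that correlation. It does not protect against correlation between different patients. At stake are the width of the confidence intervals and the type I error. Two of the three comparisons with usual care named in Study Design, M against U and MP against U, would have this structure on both sides.

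**Working it through.** **Plan's own figure.** The plan gives no ICC or design effect to reproduce. The 225 per arm is taken as stated. It does not follow from "assuming a mean difference of 1.5 and an SD of 2.4": these inputs give 41 per arm at 80% power and 54 at 90% (two-sided 5%). That is a separate matter and does not affect the steps below.

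**Inputs from the article.** Group size m = 3; 225 per arm; significance level 0.05.

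**Assumptions.** Two-sided tests; groups formed within arm; the same ICC in each exercise arm; P-group patients treated individually; ICC between 0 and 0.20, because the documents give none.

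**Step 1, design effect.** DE = 1 + (m − 1) × ICC = 1 + 2 × ICC.

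**Step 2, ratio of true to patient-level standard error.**
- Two exercise arms: r = √DE.
- Exercise arm against P: r = √((DE + 1)/2).
- The patient-level standard error is too small by 1 − 1/r.

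**Step 3, actual type I error of a nominal 5% test.** 2 × (1 − Φ(1.96/r)).

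Worked case, ICC 0.05, two exercise arms: DE = 1 + 2 × 0.05 = 1.10; r = √1.10 = 1.0488; shortfall = 1 − 1/1.0488 = 4.7%; type I error = 2 × (1 − Φ(1.96/1.0488)) = 6.2%.

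| ICC (assumed) | DE | SE too small, two exercise arms | Type I error | SE too small, exercise vs P | Type I error |
|---|---|---|---|---|---|
| 0 | 1.00 | 0% | 5.0% | 0% | 5.0% |
| 0.02 | 1.04 | 1.9% | 5.5% | 1.0% | 5.2% |
| 0.05 | 1.10 | 4.7% | 6.2% | 2.4% | 5.6% |
| 0.10 | 1.20 | 8.7% | 7.4% | 4.7% | 6.2% |
| 0.20 | 1.40 | 15.5% | 9.8% | 8.7% | 7.4% |

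**Step 4, simulation.** With 75 groups of 3 per arm (225/3), 20,000 runs and no true difference, the patient-level test between two exercise arms rejected in 5.2%, 6.2%, 7.6% and 10.3% of runs at ICC 0.02, 0.05, 0.10 and 0.20. Analysis at treatment-group level brought this back to between 4.7% and 5.2%.

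**Step 5, with the planned Bonferroni step.** Assuming six pairwise tests at 0.05/6 = 0.0083, the actual error of each test between two exercise arms is 0.0097, 0.0119 and 0.0160 at ICC 0.02, 0.05 and 0.10. Familywise error, simulated with M, MP and U clustered and P not, is about 4.2% at ICC 0, 4.6% at 0.02, 5.4% at 0.05 and between 6.6% and 6.7% at 0.10.

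**Step 6, power.** For a difference of 1.5 with SD 2.4 and 225 per arm, at 0.05/6, power is Φ(1.5/(2.4 × √(2 × DE/225)) − 2.64). It is 99.98% or more for ICC up to 0.05, and still above 99.8% at ICC 0.20.

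**The case against.** The strongest objection is that the article does not say which variable defines the GEE clusters. A GEE clustered on treatment group, with each patient's repeated measures inside it, would cover both levels and would contradict nothing in the text. A condensed article may leave that choice to a fuller plan. This stands in part: patient-level clustering is the natural reading of a section that lists only group, time and group×time, but it is inferred. The point is still more than a missing detail, because the article itself states both the grouped delivery and the effects in the model, and the two do not match.

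The second objection is size. The effect rests entirely on an ICC that the documents do not give, is small at an ICC of 0.02, is roughly halved against P, and is partly absorbed by the conservatism of Bonferroni, so that familywise error exceeds 5% only from an ICC of about 0.05. This stands, and it is why the point is conditional and modest. Bonferroni does not repair the individual intervals, which stay too narrow.

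Three stronger readings are tempting and are not supported:

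- **Fixed trios under one physiotherapist for all 16 sessions.** The article gives only the group size. It does not say that membership is fixed or that one therapist leads throughout.
- **Much larger inflation from clustering by physiotherapist.** The number of physiotherapists is not given, nor is any physiotherapist tied to a single arm. If the same therapists treat several arms, an effect common to those arms largely cancels from the comparisons between them.
- **An underpowered trial.** Step 6 shows that clustering in groups of 3 leaves power for 1.5 essentially unchanged.

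**Conclusion.** The point holds in conditional form. Exercise is delivered in groups of 3, and the stated model has no level for those groups. If patients are the GEE clusters, standard errors for comparisons involving M, MP or U are understated whenever the within-group ICC is positive. At assumed ICCs of 0.02 to 0.10 the understatement between two exercise arms is about 2% to 9%, with an unadjusted type I error per comparison of about 5.5% to 7.4%. Against P the shortfall is about half that, and at an ICC of 0 there is none.

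This rests on reading the group-of-3 sentence as covering all three exercise arms, on the patient being the GEE cluster, and, for the P comparisons, on individual delivery of pain education. The consequence is for interval width and type I error. The documents do not support a claim that the standard errors are wrong whatever the correlation.

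**What to change.** 1. Record a treatment-group identifier prospectively for every patient in an exercise arm. It may be impossible to reconstruct later.
2. State in the analysis section that the treatment group is the GEE cluster, with patients' repeated measures nested within it, and that a robust variance is used. P-group patients enter as clusters of one, or as their education-session group if they are taught in groups.
3. If membership changes over time, define the cluster as the group of first assignment.
4. Record a physiotherapist identifier and, if feasible, report a sensitivity analysis that allows for it.

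The cost is one identifier (two with the physiotherapist), a changed cluster specification and slightly wider intervals. With 225 per arm there would be 3 × 75 = 225 exercise groups plus 225 single P-group patients if pain education is individual, which is ample for a robust variance. If the ICC is near zero, the results will hardly change.

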### Data Collection

The professionals (physicians, nurses, physiotherapists, psychologists, and physical education professionals) from the health network of Pelotas City, Rio Grande do Sul, Brazil, will refer patients to the program after assessing their eligibility. Patients who show an interest in participating in the program will be marked for an initial evaluation, during which the patients will be informed about the research procedures, evaluations, interventions, and duration. After obtaining all of the necessary information, patients who wish to participate must sign the informed consent form. Only researchers will have access to the database. To maintain data confidentiality, patients will be identified by numbers.

The study protocol is shown in Figure 2. A baseline survey will be conducted after the allocation. Participants will receive questionnaires, including questions on demographic data and baseline data for outcomes.

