### The MCE Program

The purpose of the MCE program is to normalize the difficulty in the motion domain for each participant. The exercises will be divided into 3 stages of training. A progressive increase in the level of difficulty will occur as the patients correctly perform the exercises with ideal movement patterns (Table 1). A detailed anamnesis and physical examination will be performed to account for the condition of each individual participant. Additionally, these will allow us to determine the levels and goals for each stage of exercise and the progression time for each difficulty level.

In the first stage, individuals will start to learn how to perform isometric contractions of the transverse abdominis and multifidus muscles in the prone, supine, and quadrupedal positions. To ensure the correct activation of the transverse abdominis, it will be emphasized to participants that the lower part of the anterior abdominal wall (ie, below the level of the umbilical scar) should be pushed toward the spine to activate the muscle. Participants will be instructed to progressively increase the waiting time and number of contractions to up to 10 contraction repetitions×10 seconds of sustainment. At the first appointment, patients will receive awareness-raising advice for performing the deep muscle contractions and instructions on how to activate the aforementioned muscles, so that they can sustain the contractions during the exercises for about 30 to 45 minutes throughout the appointments. The patients will advance to the next stage when they show the ability to perform the exercise and control pelvic and lumbar movements with minimal effort while moving their upper and lower extremities.

In the second stage, the complexity of the exercises will be increased by progressing to functional exercises that involve performing trunk and upper limb coordination while maintaining trunk stability [15]. Patients will be taught to perform abdominal cocontraction in different postures and control movements of the lumbopelvic region with minimal effort while performing functional activities.

After learning all of the exercises in stages 1 and 2, participants will be instructed to perform trunk coordination exercises and weight loading for the upper limbs (ie, while maintaining the stability of the trunk) and consider the activities that presented difficulty or the activities for which they reported pain during implementation in the initial evaluation.

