### Outcome Measures and Assessment Points

Evaluations will be carried out before and after 8 weeks of intervention and the 12- and 24-week follow-ups. Individuals will be monitored weekly during the study period, and messages will be sent through WhatsApp (Meta Platforms) to collect information about pain intensity.

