#### Primary Outcome Measure

The primary outcome measure will be a report of pain intensity on the Numerical Pain Rating Scale [17].

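### Questionnaires that record the baseline outcomes are placed after allocation, and no described step withholds the arm until they are complete

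*Protocol article*

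**What the plan says.** All references are to the protocol article.

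- **Data Collection**, on timing: "A baseline survey will be conducted after the allocation". On content: "Participants will receive questionnaires, including questions on demographic data and baseline data for outcomes".
- **Data Collection**, on the earlier visit: interested patients "will be marked for an initial evaluation, during which the patients will be informed about the research procedures, evaluations, interventions, and duration". Consent follows. No outcome questionnaire is named at that visit.
- **The MCE Program** refers back to the same visit as one where pain was recorded: "the activities for which they reported pain during implementation in the initial evaluation".
- **Random Allocation and Blinding**: "After the initial evaluation, the participants will be allocated, through block randomization, to receive different interventions". The same section adds: "However, evaluators and patients will be blinded to the treatment groups".
- **Outcome Measures and Assessment Points**: "Evaluations will be carried out before and after 8 weeks of intervention and the 12- and 24-week follow-ups".
- **Primary Outcome Measure**: "The primary outcome measure will be a report of pain intensity on the Numerical Pain Rating Scale".
- **Statistical Analysis** takes baseline as one of the time points in a generalized estimating equation (GEE) model with group, time and group-by-time terms. It also presents the intervention effect as the post-intervention mean minus the pre-intervention mean.

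**The concern.** A baseline measurement is useful because the assigned arm cannot have influenced it. Once it is taken after allocation, that protection depends wholly on the patient not knowing the arm. Here the primary outcome is self-reported pain. Most of the secondary outcomes (disability, fear-avoidance beliefs, kinesiophobia, mood, depression, anxiety) are also questionnaires that expectation could plausibly affect.

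Patients hear about the interventions at the initial evaluation, so someone who learns their schedule could work out their arm. If that knowledge moves the answers, the arms differ at baseline for a reason other than chance. The planned change measure then counts that difference as part of the treatment effect, and no later analysis can recover the missing pre-allocation value.

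**Working it through.** **Step 1: the order of events.** The text allows two readings of the initial evaluation.

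| Reading | Support | Resulting order |
|---|---|---|
| Information and consent visit | Data Collection | initial evaluation, allocation, baseline survey |
| Clinical assessment that includes baseline | The MCE Program, which has pain recorded there | baseline before allocation, in conflict with Data Collection |

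On the first reading the sections agree, and outcome baselines definitely follow allocation. On the second they disagree. Either way the text needs correcting. The assessment schedule does not settle it, because it places the first evaluation before the intervention, not before randomisation.

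**Step 2: could a patient know the arm by then?** Under Pain Education, the P-group has two one-hour sessions. Under Random Allocation and Blinding, the M-, MP- and U-groups each have 16 sessions over 8 weeks, averaging 40 minutes. By number of sessions the P-group stands apart and the other three look alike. After allocation, participants are referred to a physiotherapist who is not blinded. Nothing says that the survey comes before that referral.

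**Step 3: how a baseline shift reaches the estimate.** For arms A and B the change contrast is

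(post_A − pre_A) − (post_B − pre_B).

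If knowledge of the arm adds b to pre_A only, the contrast moves by −b, that is, by the full amount. A group-by-time contrast of 8 weeks against baseline moves in the same way. The direct contrast post_A − post_B contains no baseline term and does not move.

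**Step 4: illustration of scale.** The plan states no figure for such a shift, so there is none to reproduce. From Sample Size Calculation: difference 1.5, SD 2.4, 225 per group. Assumed here: b of 0.3 or 0.5 points; SD 2.4 at each time point; pre-post correlation r of 0.3, 0.5 or 0.7; no true effect; normal approximation.

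- Share of the planned difference: 0.3/1.5 = 20%; 0.5/1.5 = 33%.
- Standard error of the change contrast: 2.4 × √(2(1 − r)) × √(2/225).

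| r | SE | 0.3/SE | 0.5/SE | P(reject), b = 0.3 | P(reject), b = 0.5 |
|---|---|---|---|---|---|
| 0.3 | 0.268 | 1.1 | 1.9 | 0.20 | 0.46 |
| 0.5 | 0.226 | 1.3 | 2.2 | 0.26 | 0.60 |
| 0.7 | 0.175 | 1.7 | 2.9 | 0.40 | 0.81 |

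The rejection probabilities are for a two-sided 0.05 test. At the Bonferroni level for six pairwise comparisons (0.05/6 = 0.0083) they are 0.065, 0.095 and 0.177 for b = 0.3, and 0.220, 0.334 and 0.585 for b = 0.5. These figures show only how sensitive the planned sample would be to a small shift in one arm.

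**The case against.** The strongest reply is that the protocol says patients and evaluators are blinded, and that it places the survey after allocation, not after disclosure of the allocation. If the arm stayed hidden until the forms were complete, the baseline would be sound. This stands as a condition: the risk is conditional, and the text does not show that patients know their arm when they answer. It does not remove the point, because no step is described that makes the condition hold.

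The reply is also right on the arms. A reader might picture intensive treatment set against an untreated control. Usual care is itself an exercise programme on the same 16-session schedule as the M- and MP-groups, so disappointment is much less plausible in those contrasts. The risk is clearest for comparisons with the P-group.

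Some stronger inferences are tempting, and the document does not support them:

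- **That two sections flatly contradict each other.** This depends on what the initial evaluation is, and one reading satisfies both.
- **That a baseline covariate would be contaminated.** The analysis section names none.
- **That intention to treat is undermined by withdrawals before the survey.** No such loss is documented, and multiple imputation is planned. A randomised person without a baseline value is not thereby excluded.
- **That every comparison is exposed.** The groups are also compared at each time point, and a comparison of 8-week means is unaffected.

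**Conclusion.** The point holds in a limited form. As written, the questionnaires that supply baseline outcome values come after allocation, the sequence across sections is unclear, and the stated blinding is not backed by a step that withholds the arm until the survey is complete. The change measure and the group-by-time contrast against baseline are therefore open to an avoidable bias, mainly where the P-group is involved.

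Neither the size nor the direction of that bias can be derived from the document. The range of 20% to 33% of the planned difference rests on an assumed shift of 0.3 to 0.5 points. The standard error of 0.226 further needs a pre-post correlation of 0.5, if 2.4 is the SD at a single time point. The case for correction rests on the order of procedures, which analysis cannot repair afterwards, and not on these figures.

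**What to change.** In Data Collection, replace the sentence on timing with a statement that all baseline outcome measures are completed after consent and before the allocation is generated or revealed. Release an allocation only once the baseline form is recorded as complete.

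Then make the other places agree. Outcome Measures and Assessment Points should set the first assessment relative to randomisation. Random Allocation and Blinding should say what the initial evaluation contains. Figure 2, which could not be seen for this review, needs a change only if it shows a different order.

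The cost is a few sentences and a small change in the order of procedures. The same questionnaires are used and no new measurement is added. Whether it all fits into one visit is for the investigators to confirm, since the article does not say how many visits precede treatment.
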